**Fig. 1 Fig1:**
[figure not shown]
Study flowchart

**Fig. 2 Fig2:**
[figure not shown]
Treatment schedule and outcome measures

### Statistical analysis

For all participants who satisfy the inclusion criteria and start receiving the test intervention, as a definitive statistical analysis model, ANCOVA (regression model) was used to evaluate the effect of the treatment. The outcome measure was the rate of reduction, and independent variables included the treatment method, possible confounders in randomization, and baseline measure of muscle mass and analyze the secondary endpoints in an exploratory manner.

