#### Control group

Patients will receive the conventional physiotherapy protocol alone.

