### Criteria for discontinuation

Failure to elicit palpable muscle contraction at maximum tolerable current after three daily sessions due to patient discomfortAny injury to the skin and/or striated muscleVoluntary withdrawal of consent from the trial

Rationale for criteria 1 and 2: to eliminate the influence of these factors on the evaluation of efficacy and safety.

Rationale for criterion 3: to respect participants’ voluntary decision.

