### Rationale

In a previous study of disuse muscle atrophy in patients with consciousness disturbance in the intensive care unit (ICU) [4], change in cross-sectional area was found to be 0.85 on average after 1 week of conventional rehabilitation (without EMS). The ratio of cross-sectional area pre and post intervention changed by 0.85 after 2 weeks of EMS-integrated rehabilitation (EMS group) compared with 0.72 after 2 weeks of conventional rehabilitation (control group), for a difference of 0.13 between the groups. For the present study, we recalculated the sample size for analysis of covariance (ANCOVA) with the standard deviation of 0.15 for both groups, alpha error of 0.05, power of 0.8, and covariance of 1. A sample size of 44 was required based on the calculation. Thus, we revised the manuscript to include 25 patients for each group.

To calculate sample size for the present study, we determined that approximately 25 pelvic fracture patients required 2-week hospitalization at the Department of Emergency Medicine and Critical Care, Center Hospital of the National Center for Global and Medicine between 2015 and 2016, with no dropouts including those due to death. Thus, a total of 50 patients (25 in each group) is required for the present study.

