### Missing data

While missing data were not dealt with in the present study, data may be complemented after some process as appropriate if there are a certain number of missing values.

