### Blinding

Assessor, participants, treatment team, and statisticians were unblinded.

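### The primary analysis set depends on starting treatment after open-label allocation, and the discontinuation rationale leaves open whether stopped patients are analysed, so losses could fall mainly on the EMS arm

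*Protocol article*

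**What the plan says.** Four parts of the protocol article bear on who enters the primary comparison.

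- **Statistical analysis.** The ANCOVA is run "For all participants who satisfy the inclusion criteria and start receiving the test intervention". Treatment method is one of the independent variables. The section does not say that all randomised patients are analysed, and it does not say what starting means for a control.
- **Control group.** "Patients will receive the conventional physiotherapy protocol alone". Physiotherapy is given in both arms; EMS is the added element in one.
- **Criteria for discontinuation.** There are three criteria: no palpable contraction at the highest tolerable current after three daily sessions, injury to skin or striated muscle, and withdrawal of consent. The first two are explained thus: "Rationale for criteria 1 and 2: to eliminate the influence of these factors on the evaluation of efficacy and safety".
- **Missing data.** "While missing data were not dealt with in the present study, data may be complemented after some process as appropriate", on condition that a certain number of values are missing.

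The trial is fully open. Under Blinding: "Assessor, participants, treatment team, and statisticians were unblinded". Under Allocation, the coordinator tells the investigators the result, and these investigators are the physicians in charge.

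**The concern.** The Objective asks whether adding EMS to conventional rehabilitation retards muscle loss. Randomisation protects that comparison only if patients are analysed as allocated. Here the set depends on what happens after allocation is known, and the first discontinuation criterion describes a result of being assigned EMS. A control cannot meet it. The second criterion is not restricted by arm, but the list of potential side effects names skin injury at the belt site, so it is more likely under EMS. The Discussion also expects patients to differ when contractions cause pain.

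If such patients leave the comparison, the remaining EMS arm is selected for tolerance and response, while the control arm stays nearly whole. The estimate would then describe EMS in those who tolerate it, not the effect of assigning EMS. With 25 per arm, a few patients matter. Because the documents support two readings, staff who know the allocation could end up choosing between them after seeing the data.

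**Working it through.** **1. The text applied to each type of patient**

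| Patient | Statistical analysis section | Discontinuation rationale | If the day 14–17 CT is absent |
|---|---|---|---|
| Allocated to EMS, never started | Out | Silent | Out |
| Allocated to control, physiotherapy started | In, if the test intervention is taken to mean the assigned treatment | Silent | Out of the ANCOVA unless completed by an unspecified process |
| EMS stopped after three sessions, no contraction | In (has started) | Points to out | Same |
| EMS started, then skin or muscle injury | In (has started) | Points to out | Same |

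The first row is a post-randomisation exclusion on any reading. The last two rows are where the sections conflict.

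**2. The plan's own figure**

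Inputs from Rationale: "for a difference of 0.13 between the groups", SD 0.15, alpha 0.05 (taken as two-sided), power 0.80.

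- Normal approximation: n per arm = 2 × (1.960 + 0.842)² × (0.15/0.13)² = 20.9, so 21 per arm and 42 in total.
- Two-sample t-test: 21.9, so 22 per arm and 44 in total. This matches the stated 44.
- At 25 per arm, t-test power is 0.851.

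The sample size section is used here (25 per arm); the Abstract gives 40 in total.

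**3. Size of the bias if EMS patients are lost**

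The documents give no EMS discontinuation rate and no correlation between tolerance and outcome, so both are assumptions. Let there be no true effect, lose the k of 25 EMS patients with the lowest tolerance, and let tolerance correlate r with the post/pre area ratio. With f = k/25 and z the normal quantile of f:

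bias = r × 0.15 × φ(z)/(1 − f)

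Example, k = 3 and r = 0.5: f = 0.12, φ(z)/(1 − f) = 0.2000/0.88 = 0.227, bias = 0.5 × 0.15 × 0.227 = 0.017.

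| k lost | Bias, r = 0.3 | Bias, r = 0.5 | Type I error, r = 0.3 | Type I error, r = 0.5 |
|---|---|---|---|---|
| 1 | 0.004 | 0.007 | 0.053 | 0.055 |
| 2 | 0.007 | 0.012 | 0.051 | 0.058 |
| 3 | 0.010 | 0.017 | 0.055 | 0.067 |
| 5 | 0.016 | 0.026 | 0.063 | 0.087 |

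Type I error is two-sided, from 20,000 simulated trials per cell with a t-test. Simulated biases agree with the formula to within about 0.002. Against the planned effect, 0.004/0.13 = 3% and 0.026/0.13 = 20%. At r = 0 the bias is zero. At r = 1 with k = 5, an unrealistic extreme, the bias is about 0.053 and type I error 0.239.

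**4. Power if everyone is kept**

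If k of 25 EMS patients gain nothing, the mean difference is 0.13 × (1 − k/25). For k = 3 this is 0.1144. t-test power at 25 per arm:

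| k without benefit | 0 | 1 | 2 | 3 | 5 |
|---|---|---|---|---|---|
| Power | 0.851 | 0.822 | 0.789 | 0.752 | 0.671 |

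**The case against.** The strongest reply is that stopping treatment is not exclusion from analysis. No sentence removes stopped patients or cancels their CT, and a patient who meets the first criterion has by definition had three sessions. Read literally, the analysis section keeps that patient. This stands: exclusion of stopped patients is an inference from the rationale and the missing-data text, not a stated rule. What remains is that the rationale says the opposite of what the analysis section implies.

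A reader might go further in four ways that the documents do not support.

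- *That the set contains only EMS patients, since controls never receive the test intervention.* Treatment method is a model term, which requires both arms. The phrase probably means the assigned treatment. The set still depends on starting.
- *That losses fall on the EMS arm alone.* Only the first criterion is specific to EMS. Injury is not restricted by arm, withdrawal applies to both, and a control who does not start would also be dropped.
- *That bias toward EMS is established.* It needs poor tolerance to go with greater muscle loss. That is plausible, but the documents give no figure.
- *That the safety summary would omit injured patients.* Serious adverse events are recorded from consent to day 14 regardless of cause, with no link to the analysis set. Non-serious events are not recorded because the adverse-event section says so, which is a separate matter.

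It is also fair that a condensed article may leave follow-up after stopping to the full protocol, and that the missing-data text allows some completion. The point therefore rests on the stated set and the stated rationale, not on what is absent.

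**Conclusion.** The point holds as a defect in the stated primary analysis. The set is not defined by randomisation in a trial where everyone knows the allocation, and the discontinuation rationale conflicts with the analysis section over patients who start and then stop. Losses could fall mainly on the EMS arm and would probably favour EMS.

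Under 1 to 5 losses at a correlation of 0.3 to 0.5, the effect runs from negligible (one patient, type I error near nominal) to material (a fifth of the planned difference, type I error near 0.09). These figures assume that all losses come from the EMS arm and use a t-test in place of the ANCOVA. Direction is probable, not proven, and the planned sample size of 44 is not in question.

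**What to change.** - **Statistical analysis:** replace the definition of the set with, for example: *All randomised patients are analysed in the arm to which they were allocated, whether or not the allocated treatment was started or completed.* Keep the current set as a sensitivity analysis, saying what starting means in each arm.
- **Criteria for discontinuation:** leave the criteria as they are. Delete the rationale about removing their influence on the evaluation of efficacy. State that stopped patients still have the scheduled day 14–17 CT and secondary measurements unless they withdraw consent to follow-up.

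The cost is a few sentences and no new procedure, since the CT is already scheduled. The estimate may be less favourable to EMS. If 3 of 25 EMS patients gain nothing, power falls from about 0.85 to about 0.75, below the planned 0.80. That is the power for the effect of assignment, and the sponsor should decide knowingly whether 25 per arm is still enough.

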### Missing data

While missing data were not dealt with in the present study, data may be complemented after some process as appropriate if there are a certain number of missing values.

### Blinding

Assessor, participants, treatment team, and statisticians were unblinded.

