### Outcomes

#### Primary endpoint

Change in cross-sectional area of thigh muscle between pre and post intervention, as measured on CT images

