#### Secondary endpoints

We will measure all secondary endpoints on the same dates that CT imaging is obtained.Change in cross-sectional area of calf muscle between pre and post intervention, as measured on CT imagesReduction in thigh and calf circumference, measured at the same sites as CT image measurementsThigh and calf circumference measured on CT imagesChanges in manual muscle testing results

We will obtain baseline CT data of the region including the pelvis and lower extremities at the time of admission (pre intervention, from day − 4 to day 0) and measure cross-sectional area of the thigh and calf muscles. Day 1 is defined as the first day of rehabilitation intervention.

To evaluate the outcomes of intervention, we will obtain post-intervention plain CT data of the region including the pelvis and lower extremities and measure cross-sectional area of the thigh and calf muscles on day 14 of intervention (or before the end of day 17). Specifically, we will obtain the following measurements.Thigh: height at the center of a line linking the greater trochanter and knee joint cleftCalf: height at the center of a line linking the fibular head and external condyleThigh and calf muscle cross-sectional area: we will extract areas with intensity in the range of 30 to 100 Hounsfield Units (HU) from CT slices and measure cross-sectional area to determine change between pre- and post-intervention values

We will obtain CT scans in the supine position with both legs in the neutral position, with a pillow placed under both legs to avoid compression of the posterior aspect of the legs from the CT bed. We will ask patients to relax to minimize the influence of morphological changes due to muscle contraction. The following CT machines will be used:Aquilion™ CX TSX-101A/NA, Application Ver. V4.62JR019 (Toshiba Medical Systems Corp., Tokyo, Japan)SOMATOM Definition Flash VA44A, Somaris/7 Syngo CT 2012BWinNT 6.1, Service Pack 1, VA44A_08_P16 (Siemens Healthcare, Forchheim, Germany)Aquilion ONE™ TSX-301A/2A, Application Ver. V4.7JR004 (Toshiba Medical Systems Corp.)Discovery CT 750HD, Application Software, 11 MW44.11.V40_PS_HD64_G_GTL (General Electric Healthcare, Waukesha, WI, USA)

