### Evaluation and reporting of adverse events

#### Definition of adverse events

Serious adverse eventsWe will record any adverse event listed below, occurring in the period between the date of providing informed consent and day 14, irrespective of the presence or absence of a causal relationship. Also, we will promptly report any occurrence to the head of the research institute via the reporting division of the hospital within 7 days after the serious adverse event is first noticed.Serious adverse events:Resulting in deathBeing life-threateningRequiring inpatient hospitalization or prolongation of existing hospitalizationResulting in persistent or significant disability/incapacityResulting in congenital anomalyOther adverse eventsThe therapeutic devices that will be used in this study have already been approved and are routinely used in the clinical setting. Thus, we will not record non-serious adverse events.We will use the designated case report form to record case information. We will register the case information digitally, with the principal investigator assigning the case number. After registration, the principal investigator and an analyst will analyze individual cases. They will pass the analysis report to the planning and strategy manager.

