## Discussion

Population aging is progressing worldwide, and the number of aged patients with fracture of the femur or pelvis due to falls or traffic accidents has been increasing. Muscle atrophy in patients with femoral fracture can be minimized by physiotherapy with a specific load early after operative fixation if performed soon after the accident. However, regardless of early fixation, patients with severe pelvic fracture may need long-term bed rest because a gravitational load cannot be applied for a relatively long time. This causes marked reduction of muscle mass of the lower extremities. EMS is applicable to such patients, and our study may provide evidence that EMS can prevent muscle atrophy to some extent and will provide an alternative to rehabilitation for these patients. Therefore, it is worthwhile to conduct this study.

Finally, we discuss the potential limitations of the study. First, we think that differences among individuals may emerge when muscles contractions cause pain. To solve this problem, we will provide patients with sufficient analgesics, gradually increasing the dose as needed. A second limitation is that this study is open-labeled. We think that there is a possibility that patients of controls have slower rehabilitation than those of receiving EMS, and thus bias due to unblinding might persist. However, it is impossible to hide which allocated patients receive EMS because patients can feel when their muscles are stimulated (Additional file 1).

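### The assessor is left unblinded without a stated reason, although the CT images behind the primary endpoint could be read without knowledge of allocation

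*Protocol article*

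**What the plan says.** The Blinding section is one sentence: "Assessor, participants, treatment team, and statisticians were unblinded". It gives no reason for any of the four groups.

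The Discussion returns to the matter as a limitation. It concedes that "thus bias due to unblinding might persist", linking this to slower rehabilitation among controls, and then explains why masking was not attempted: "it is impossible to hide which allocated patients receive EMS because patients can feel when their muscles are stimulated". Bias in measuring the outcome is not mentioned.

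The primary endpoint is "Change in cross-sectional area of thigh muscle between pre and post intervention, as measured on CT images". The measurement rules stand under Secondary endpoints. The thigh level is the midpoint between the greater trochanter and the knee joint cleft, and for the area "we will extract areas with intensity in the range of 30 to 100 Hounsfield Units (HU) from CT slices". Patient positioning is standardized as well. The post-intervention scan is taken on day 14, or by the end of day 17.

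No CT reader is named. The nearest statement, in the section on adverse events, is that after registration of the case information "the principal investigator and an analyst will analyze individual cases". No masked, independent or duplicate reading is described.

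**The concern.** Open-label treatment cannot be avoided here, but open reading of a stored image can. A reason that holds only for people who feel or deliver the stimulation has been left to stand for everyone, including whoever measures the images.

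What is at stake is the primary comparison. A reader who knows the arm may, without intent, place a landmark or pick a slice in a way that favours one group. An error of this kind is systematic between arms. A larger sample does not average it out, and adjustment for baseline muscle mass in the ANCOVA does not remove it. In a single-center, open-label trial, masked reading is one of the few protections for the primary result still available.

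**Working it through.** **Step 1. Does the stated reason reach the reader?**

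| Group listed as unblinded | Covered by the Discussion's reason? |
|---|---|
| Participants | Yes, they feel the stimulation |
| Treatment team | By extension, since they apply it |
| Assessor | Not when measuring stored CT images |
| Statisticians | No |

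**Step 2. How much discretion does the reader have?**

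- Area extraction follows a fixed window of 30 to 100 HU, which leaves little room for judgement.
- The level is fixed by rule as a midpoint, but a person must locate both landmarks and select the slice.
- The follow-up scan comes after allocation is known. The baseline scan (day −4 to day 0) might be measured before allocation; the protocol does not say. Even then, the follow-up half of the change stays exposed.

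**Step 3. Reproduce the plan's own figure.** Inputs from the sample size Rationale: difference 0.85 − 0.72 = 0.13, SD 0.15, alpha 0.05 (taken as two-sided), power 0.8, one covariate.

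- Normal approximation: 21 per arm, 42 in total.
- Two-sample t-test: 21.9, so 22 per arm and 44 in total.
- ANCOVA with one covariate and no variance reduction, 22 per arm: power 0.801.

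The stated 44 is reproduced. With the target of 25 per arm, power is about 0.85. Masking the reader changes none of these figures.

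**Step 4. How sensitive is the test to a reading tilt?** The documents give no reading error, so the tilt b is an assumption: a systematic between-arm shift in the post/pre area ratio when the true effect is zero.

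- Standard error: SE = 0.15 × √(2/25) = 0.0424.
- Noncentrality: b / SE.
- Rejection probability: both tails of the noncentral t with 50 − 3 = 47 df (one covariate), critical value 2.012.

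| Assumed tilt b | Share of planned 0.13 | b / SE | Two-sided type I error |
|---|---|---|---|
| 0 | 0% | 0 | 0.050 |
| 0.01 | 8% | 0.24 | 0.056 |
| 0.02 | 15% | 0.47 | 0.075 |
| 0.03 | 23% | 0.71 | 0.107 |

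With 48 df (no covariate) the results agree to three decimals. The table shows how the test responds if a tilt exists. It is not an estimate of any tilt.

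**The case against.** **The measurement is largely rule-based.** The level is defined by landmarks, the area by a fixed HU window, and positioning is standardized. This stands in large part and means that the bias may be small. It does not remove the human step of placing landmarks and choosing the slice.

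**The tilt sizes have no support in the documents.** This stands in full. At 0.01 the inflation is trivial, and nothing shows that 0.02 or more is to be expected. The planned difference is also not small: 0.13/0.15 is about 0.87 SD, and 0.13/0.0424 is about three standard errors at 25 per arm. A reader might infer that the primary result is likely to be distorted, or that the plan cannot go ahead unchanged. The documents support neither.

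**The assessor may not be the CT reader.** Limb circumference and manual muscle testing are assessed on the patient, and the protocol does not say who measures the scans, or when. So it is not established that the reader knows both arm and time point. But the primary endpoint is a CT measurement and no masked reader is described, so reading the sentence to include the CT reader is reasonable. If a masked reader does exist, the sentence misdescribes the trial and needs correcting anyway.

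**The limitation is disclosed.** The trial is called open-label throughout, and the Discussion defends open-label treatment rather than open CT reading. That is fair. The accurate statement is that no reason is given for the assessor. Disclosure is enough for what cannot be avoided, and open reading can be.

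**Conclusion.** The point holds as a statement about exposure. The plan chooses an unblinded assessor, gives no reason that applies to reading stored images, and describes no masked reading, so the primary endpoint is open to avoidable differential reading. Because the protocol states this choice outright, it is not a detail left to a fuller document.

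The size is unknown. The type I errors in the working rest on assumed tilts, on SD 0.15 and 25 per arm from the protocol, and on a two-sided 5% test. The conclusion also assumes that the assessor in the Blinding section includes whoever measures the scans. On that basis the change should be made because it is cheap and removes a needless weakness, not because the documents show a material bias.

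**What to change.** Reword the Blinding section so that only participants and the treatment team are unblinded. Add that CT images are de-identified, given a random code and measured without knowledge of allocation by whoever in the study team reads them, and that someone other than the reader holds the code list until all measurements are locked. In the Discussion, limit the statement that allocation cannot be hidden to participants and the treatment team.

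Two additions are optional: masking the order of the scans, and giving the statistician coded arms until the primary analysis is locked.

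The cost is a small effort for coded export and for keeping the code list. It needs no extra scan and leaves the sample size unchanged. No extra reader is needed either, provided that the person who reads does not hold the code list. This proviso needs checking: the Confidentiality section makes the principal investigator responsible for storing the random number table, and the principal investigator is also one of the two people said to analyze individual cases. If that role includes measuring the scans, the tasks must be divided. Because the scans are stored, masked reading can be adopted even after enrolment has begun.
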